## Abstract

**Background:** Flexor spasticity of the upper limb is common in poststroke patients and seriously affects the recovery of upper limb function. However, there are no standard management protocols for this condition. Radial extracorporeal shock wave therapy (rESWT) is widely used for various diseases, some studies reported the effects of ESWT on reducing spasticity, but the mechanism of ESWT to reduce spasticity by affecting the excitability of stretch reflex or non-neural rheological components in spastic muscles or both is not yet clear. A large randomized controlled trial with comprehensive evaluation indicators is still needed. The study is to observe the effect of rESWT on flexor spasticity of the upper limb after stroke and explore its mechanism.

**Methods:** A prospective, randomized, double-blind controlled trial is to be performed. One hundred participants will be recruited from the Inpatient Department of Zhujiang Hospital. Eligible patients will be randomly allocated to either receive three sessions of active rESWT (group A) or sham-placebo rESWT (group B) with 3-day intervals between each session. Assessment will be performed at baseline and at 24 h after each rESWT (t1, t2, and t3). The primary assessment outcome will be the Modified Ashworth Scale, and other assessments include surface electromyography, MyotonPRO digital muscle function evaluation, and infrared thermal imaging. All data will be analyzed using intention-to-treat principles. Multiple imputation by chained equations will be used to address missing data caused by loss to follow-up and nonresponses. Per protocol, analyses will also be performed on the participants who complete other assessments. Statistical analysis will be performed using SPSS software (version 20.0) and the significance level set at *p* < 0.05.

**Discussion:** This trial aims to analyze the application of rESWT for the management of spasticity after stroke *via* appropriate assessments. We hypothesized that after receiving active rESWT, patients would show greater improvement of upper limb muscles compared with patients within the sham-placebo group. The rESWT would be an alternative to traditional methods, and the results of this study may provide support for the further study of potential mechanisms.

**Clinical Trial Registration:**www.chictr.org.cn, identifier: ChiCTR1800016144.

## Background

Spasticity is a form of muscle hypertonia that results in the pyramidal tract when corticoreticulospinal fibers (extrapyramidal tract) are damaged, which gives an upper motor neuron syndrome due to a lesion of the central nervous system (brain and/or spinal cord) (1). After central nervous system injury, the inhibition of cerebral cortex and other higher centers is lost, and the excitability of γ-motor neurons is enhanced so that the excitability and sensitivity of muscle spindle are increased. Through the α-γ loop, the α-motor neurons in the anterior horn of the spinal cord are overexcited, resulting in an excessive increase in the stretch reflex. Continuous contractions of spasmodic muscles can lead to contracture, pain, limited joint movement, and joint deformity (2). Flexor spasticity is common in poststroke patients with upper limb dysfunction, and uncontrolled spasticity often leads to secondary complications such as pain and contractures (3) while placing a significant mental and financial burden on the patient, caregivers, and society (4). The mechanisms underlying this disorder may be due to the hyperexcitable stretch reflexes caused by the imbalance of supraspinal inhibitory and excitatory inputs after the upper motor neuron lesion (1) and also involve the changes in muscle properties (5, 6) (e.g., stiffness, fibrosis, and atrophy), which is referred as intrinsic hypertonia. Aggressive and appropriate spasticity management contributes to motor relearning and function recovery during chronic stages (4, 7). Currently, mainstream interventions for upper limb hypertonia include stretching, oral anti-spasticity medications, focal botulinum toxin (BTX) injections, and surgical treatment (7–10). However, the treatment methods mentioned earlier have advantages or drawbacks in their effectiveness and safety (8, 11–13). For example, BTX injection therapy is more effective but invasive and more expensive. Surgical treatment is more traumatic, and the risk is higher.

An extracorporeal shock wave is defined as a sequence of single sonic pulses with high peak pressure (14, 15), which can cause energy gradient differences and torsional tension between tissues of different densities through energy conversion and transmission, and form a cavitation effect, which induces a biological effect (16). During the past few decades, extracorporeal shock wave lithotripsy (17) has been widely used and has evolved to be standard therapy used for urinary calculi due to its excellent efficacy, non-invasiveness, and lack of obvious complications. At present, extracorporeal shock wave therapy (ESWT) has also been widely used for the treatment of various neurological and musculoskeletal diseases (18, 19), such as cerebral palsy (20), multiple sclerosis (21), tendinopathy (22), chronic tennis elbow (23), and nonunion of long bone fracture (24). Recently, several studies (25–27) have indicated that ESWT could be used for decreasing hypertonia in strokes. However, only a few convincing studies have been published; a systematic review (28) in 2020 evaluated the scientific reliability and methodological quality of recent clinical trials according to their level of evidence and found that among enrolled 17 studies, only seven studies obtained Sackett's grading system's highest level 1 of evidence (studies scoring 6–10). A most recent overview (29) in 2021 concluded that an ESWT effectively reduced spasticity after stroke without adverse effects, but the mechanism of action of ESWT on spasticity muscles and standard parameters of ESWT (regarding frequency, energy flux density, location, and total ESWT sessions) in poststroke spasticity remained unclear. Therefore, a prospective large-sample randomized, double-blind controlled trial with a comprehensive assessment method is needed to further confirm its efficacy and explore the underlying mechanism of ESWT on spasticity. There are two types of ESWT: focused extracorporeal shock wave therapy (fESWT) and radial extracorporeal shock wave therapy (rESWT). According to differences of mechanical properties in fESWT and rESWT and combine the study outcomes of Wu et al. (30), which was the only one to directly compare the effect of rESWT and fESWT so far, we chose rESWT device for the management of upper limb spasticity after stroke in this study.

The Modified Ashworth Scale (MAS) (31, 32) is the most widely used clinical scale to grade spasticity and shows high inter- and intra-rater reliability for the assessment of muscle tone of upper extremities. H reflex can objectively evaluate changes in the excitability of α-motor neurons before and after treatment. Motor nerve conduction velocity (MCV) is a diagnostic technique used to assess peripheral nerve conduction function. By detecting the MCV of the median nerve before and after rESWT intervention, we can observe whether the peripheral nerve has been damaged and determine the safety of the ESWT procedure. Surface electromyography (sEMG) can reflect the overall situation of muscle activity by placing surface electrodes on the muscle to collect electrical signals (33). The sEMG indexes of root mean square (RMS), integrated electromyogram (iEMG), and co-contraction ratio (CR) (34–36) can be used to assess muscle spasms objectively and quantitatively. The MyotonPRO digital muscle function assessment system is a new non-invasive instrument that can be used to evaluate the functional status of skeletal muscles and biological soft tissue. It can quantitatively measure muscle tension, elasticity, stiffness, and other functional conditions (37, 38). A previous study by Dymarek et al. (39) has shown that ESWT can improve trophic conditions of spastic muscles. The infrared thermal imaging (IRT) system detects local trophic condition changes in spasmodic muscles of the upper limbs, which are associated with blood microcirculation and surface temperature distribution (40, 41). The assessment techniques mentioned earlier can reflect the changes of upper limb spasm, muscle tension, nerve excitability, muscle elasticity, and surface temperature of stroke patients from different perspectives and can comprehensively reflect the effects of ESWT from multiple perspectives. Therefore, this trial is designed to use the assessment techniques mentioned earlier to examine the efficacy (rESWT can relieve upper limb spasticity after stroke) and safety (rESWT has no harm to nerve, muscle, and other tissues and organs) of rESWT for the treatment of upper limb spasticity after stroke.

## Methods/Design

### Trial Design

This study is a prospective, double-blind, and randomized controlled trial that conformed to Standard Protocol Items of the Recommendations for Interventional Trials guidelines (42) (Additional file 1). The flow diagram of the study to be followed in this study is shown in Figure 1. The participants are observed during their hospital stay and are randomly assigned to either receive three rounds of treatment with active rESWT (group A) or sham-placebo rESWT (group B). Assessments including MAS, H reflex, MCV, sEMG, myotonometer, and IRT are to be performed at baseline and at 24 h after intervention.

**Figure 1 F1:**
[figure not shown]
CONSORT flow diagram of study.

### Study Setting

The study setting is the Department of Rehabilitation Medicine at the Zhujiang Hospital of Southern Medical University, Guangzhou, China. The first patient was recruited on October 18, 2018, and the recruitment was planned to be completed within 3 years.

### Patient and Public Involvement

To have scientifically rigorous clinical trials and reliable results, patients in this trial will not be involved in the design, recruitment, or conduction of the study. After the last visit, the patients will be informed by the study's physician of the results in the form of pictures and text.

### Inclusion Criteria

Participants will be qualified for inclusion when they meet the following criteria: (1) meeting the “criteria for the diagnosis of cerebrovascular diseases” adopted by the Fourth Academic Conference on Cerebrovascular Diseases in 1995 (43) and confirmed using computed tomography or magnetic resonance imaging examination of the head; (2) age between 35 and 75 years old, with a first episode > 1 month and being in a stable clinical condition; (3) the presence of hemiplegic or hemiparesis with elbow joint spasticity grade > 1, determined by MAS (31); (4) no obvious cognitive impairment; and (5) the informed consent form being completed by the patient.

### Exclusion Criteria

The exclusion criteria are as follows: (1) having received oral antispasmodic drugs, BTX injections, and local block or surgical treatments for decreasing spasticity; (2) fixed elbow joint muscle contracture; (3) uncontrolled hypertension; (4) patients with chronic heart failure, malignant arrhythmia, and other severe organic heart diseases; (5) patients with a pacemaker and other electronic implants; (6) the presence of coagulation dysfunction; (7) patients with local infections and skin rupture; and (8) refusal to participate in this study.

### Interventions

**Active Radial Extracorporeal Shock Wave Therapy Intervention (Group A):** An rESW device (Power Shocker LGT-2510A, Guangzhou Longest Science & Technology Co., Ltd., China) was used for shock wave therapy. Study participants were treated in the supine position on the area of the biceps brachii, the flexor carpi radialis, and the pronator teres muscle after their affected side has been marked and the skin has been cleaned by soaking with alcohol.

The coupling gel as a contact medium is evenly applied onto the treatment probe to reduce tissue resistance, and a medium- to high-intensity pressure was applied to keep the probe close to each muscle belly. The following protocol is to be used: 2,000 shots, an energy flux density of 0.03 mJ/mm^2^, a pressure of 0.2 MPa (two bars), and a frequency of 8 Hz is delivered to each marked position, for a total of three rounds of treatment, once in 3 days.

**Sham Radial Extracorporeal Shock Wave Therapy Intervention (Group B):** The protocol to be used is the same as that of “group A,” except that pressure is one bar and no coupling gel is used on the treatment site, whereas a thick layer of gauze is placed between the skin and the probe instead, with no pressure applied.

The physiotherapist who is to perform the intervention should have received standardized training and must be familiar with the process and details of the intervention. The patients are all required to undergo the same routine therapeutic program (including common physical therapy and occupational therapy).

### Outcome Measures

#### Primary Outcome Measure: Modified Ashworth Scale

The scale is graded in six stages, ranging from 0 (no increase in tone) to 4 (limb rigid in flexion or extension). For the convenience of statistical analysis, a MAS grade of 1+ is to be substituted with a value of 2, whereas grades 2, 3, and 4 are to be substituted with values of 3, 4, and 5, respectively Table 1.

**Table 1 T1:** Definitions of MAS for grading muscle spasticity.

**Grade**	**Modified ashworth scale (28)**	**Values**
0	No increase in muscle tone;	0
1	Slight increase in muscle tone, manifested by a catch and release or by minimal resistance at the end of the range of motion when the affected part is moved in flexion or extension;	1
1+	Slight increase in muscle tone, manifested by a catch, followed by minimal resistance throughout the remaining (less than half) range of motion;	2
2	More marked increase in muscle tone through most of the range of motion, but affected part easily moved;	3
3	Considerable increase in muscle tone, passive movement difficult;	4
4	Affected part(s) rigid in flexion or extension.	5

*For convenience of statistical analysis, a Modified Ashworth Scale grade 1+ is to be substituted with a value of 2, and grade 2, 3 and 4 are matched to 3, 4, and 5, respectively*.

(1) Recovery: Muscle tension had completely returned to normal;(2) Obvious effect: The muscle tension had not returned to normal, but muscle tension had decreased by two levels;(3) Effective: Muscle tension had decreased by 1 level;(4) Inefficacy: No change in muscle tone pre- and posttreatment.

#### Secondary Outcome Measures

Electromyography (EMG), surface electromyography (sEMG), MyotonPRO digital muscle function evaluation system, and infrared thermal imaging (IRT) are to be used for the evaluation.

**H reflex:** H reflex of the median nerve is to be detected using the Schwarzer topas EMG system (Natus Medical Incorporated, Pleasanton, CA, USA). The recording must be conducted from the flexor carpi radialis as follows: the recording electrode is to be placed at the mid-upper 1/3 junction of the medial humeral epicondyle and the radial styloid process line, the reference electrode is to be placed at the tendon, the ground electrode is to be placed at the olecranon, and the stimulation electrode is to be placed at the median nerve proximally to the elbow. The maximal amplitude of H-reflex (H-max) and M-response (M-max) are to be recorded. The H-max/M-max value, which can reflect the excitability change of the α-motor neuron, is to be calculated to detect changes in response to the effect of rESWT on the spasmodic muscle.**Motor Nerve Conduction Velocity:** The same apparatus is to be used, but the electrodes are to be placed differently. The recording electrodes must be placed on the abductor pollicis brevis muscle belly, and the stimulating electrode must be placed on the median nerve at wrist and elbow level to record distal motor latency, MCV, and amplitude. This assessment is aimed at determining whether rESWT causes nerve injury and evaluating its safety.**Root-Mean-Square Value:** An sEMG recording is to be obtained using bipolar Ag/AgCl surface electrodes (MyoMove, Northam Electric Co., Ltd., Shanghai, China) for the sEMG assessment. The patient is to be treated while in a sitting position. The electrodes are to be placed on the fullest part of the upper limbs muscle belly. The locations at which the stimulating and recording electrodes are to be placed must be rubbed with 70% alcohol to reduce skin impedance. Electrode placement is to be done as recommended by Surface EMG Non-invasive Muscle Assessment and the International Society of Electrophysiology and Kinesiology. With the upper limbs of a patient comfortably placed on the treatment table, the resting sEMG activity of the musculus biceps brachii (BM) and flexor carpi radialis are to be measured under stable and static conditions for 30 s at a time. Also, the RMS of biceps brachii and flexor carpi radialis is calculated. RMS can be used to objectively and quantitatively evaluate the condition of muscle spasms, with a higher value indicating a more severe muscle spasm.**Integrated Electromyogram and Co-contraction Ratio:** The patient is seated with the upper body fixed to the seat with a wide nylon strap. The elbow of the patient is at a 45° flexed position and wrist in a neutral position, and the hand holds the handle of the arm strength test joystick of Biodex System 3® dynamometer (Biodex Medical Systems, Shirley, NY, USA). The electrodes are to be placed on the muscle belly of BM and musculus triceps brachii (TM). Training is to be performed for 1 min before the assessment to help patients familiarize themselves with the process. During the test, the patients are to be asked to stretch the elbow joint with maximum strength for 10 s to measure maximum isometric voluntary contraction (MIVC) of TM (44). The iEMG and CR of BM and TM are to be recorded for 20 and 5 s before and after contraction, respectively, as the basic control. The test is to be carried out three times, with an interval of 5 min between each application, and the maximum value is to be recorded. The assessment includes the iEMG of the BM and TM when the elbow is stretched for MIVC, and then the CR is calculated. The iEMG value can reflect the total amount of muscle discharge per unit time and is mainly used to analyze the contraction characteristics of muscles per unit time. CR refers to the proportion of antagonist muscles during the process of active muscle contraction (34), although it is well known that increased synergistic contraction of antagonistic muscles is a common phenomenon in stroke patients. The decrease of CR within MIVC of the elbow indicates a reduction in the strength of the biceps tendon.
$$\begin{array}{l} \text{CR}=\frac{\text{iEMG of BM }}{\text{iEMG of BM }+\text{ iEMG of TM}}\times 100\% \end{array}$$**MyotonPRO Digital Muscle Function Assessment System:** The MyotonPRO system (Muomeetria Ltd., Tallinn, Estonia, EU) performs a noninvasive measurement of the functional state of skeletal muscles and biological soft tissues, which can quantitatively assess the functional status of muscle tension and elasticity (45, 46). The patient is asked to completely relax while lying in the supine position on a mat, with the forearm in the mid position and the elbow joint extended (if the muscles cannot be fully extended, the forearm is supported on both sides to maintain the forearm neutral position). The measurement point of the BM is tested perpendicular to the skin surface. Measurement is taken once every 1 min, for three times in total, and the average is obtained. The parameters required are (47): F—natural damped oscillation frequency (hertz) to describe muscle tension; C—Creep is the ratio of muscle relaxation time to deformation time, also called Deborah number; R—Muscle internal mechanical pressure release time (millisecond); and C and R reaction to the viscoelasticity of the muscle.**Infrared Thermal Imaging:** A non-invasive and non-contact infrared thermal imaging system (Baotonghua Medical Devices Co., Ltd. Chongqing, China) is to be used to detect changes in local trophic conditions related to blood microcirculation and surface temperature distribution. The instrument has a thermal sensitivity of 0.1 °C. Before measurement, all clothes covering the area to be examined must be removed, and the patients are allowed to adapt to the room for 15–20 min. The room is to be kept quiet with a temperature ranging from 22 to 27 °C and relative humidity below 45%. Then, a thermovision camera is positioned perpendicular to the area of the biceps surface on the anterior side of the arm at a distance of 1 m. The IRT value is obtained in degrees Celsius. The lower the surface temperature, the worse local blood circulation and trophic conditions of muscles.

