### Statistical Methods

The primary comparisons for MAS will be made using repeated measures mixed-effect model with terms of treatment, time, and corresponding baseline values as covariates. We will first examine the intervention by time interaction and then proceed to the main effects model with only group and time.

Repeated analysis of variance with *post-hoc* test will be used to compare changes between active rESWT intervention and sham rESWT intervention groups from baseline to the end of follow-up when data are normally distributed, and the Mann–Whitney U-test will be used when data are not normally distributed. A chi-square test will be used for dichotomous variables.

In secondary analyses, repeated measures mixed model will also be used to examine the associations between treatments and repeated measures outcomes. Additionally, linear regression and/or logistic regression analyses will be used to assess the associations between treatments and changes or increases in outcomes from baseline to the end of follow-up in univariate and multivariate modeling adjusted for relevant covariates.

All data will be analyzed using intention-to-treat principles. Multiple imputation by chained equations will be used to address missing data caused by loss to follow-up and non-responses. Per protocol analyses will also be performed in the participants who complete other assessments, including Hmax/Mmax, MCV, RMS, iEMG, CR, MyotonPRO, and IRT. Statistical analysis will be performed using SPSS software (version 20.0) and the significance level set at *p* < 0.05.

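### RMS, iEMG and CR are compared as changes from baseline, with a baseline covariate stated only for MAS; using each outcome's own baseline in the planned mixed model would be more precise at no cost (minor)

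*Protocol article*

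**What the plan says.** **Measurement (Protocol article, Secondary Outcome Measures; Table 2).** RMS, iEMG and CR are scheduled at baseline, t1, t2 and t3.

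- For the resting RMS recording, "The electrodes are to be placed on the fullest part of the upper limbs muscle belly". The same paragraph adds that "Electrode placement is to be done as recommended by Surface EMG Non-invasive Muscle Assessment and the International Society of Electrophysiology and Kinesiology", and that the skin at the electrode sites "must be rubbed with 70% alcohol to reduce skin impedance".
- For iEMG and CR the wording differs: electrodes go on the muscle belly of biceps and triceps. The paragraph also provides a within-session reference recording before and after contraction, and three trials of which the maximum is kept.
- No normalisation of RMS or iEMG across visits is stated. The article neither describes nor rules out keeping the same electrode site between visits.

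**Analysis (Protocol article, Statistical Methods).**

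- MAS has a repeated-measures mixed model with treatment, time and baseline value.
- The next paragraph names no outcomes. There, repeated ANOVA under normality, or Mann–Whitney otherwise, "will be used to compare changes between active rESWT intervention and sham rESWT intervention groups from baseline to the end of follow-up". Since MAS already has its own model, the natural reading is that this governs the other continuous outcomes.
- Secondary analyses add a repeated-measures mixed model for the repeated outcomes, without restating a baseline covariate. They also add linear or logistic regression adjusted for covariates that are not named.

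**The concern.** Surface EMG amplitude varies from day to day within a patient, partly for biological reasons and partly because electrodes may not sit in exactly the same place. A change score subtracts one noisy reading from another, so it carries the error of both. A model that uses the baseline reading as a covariate weights it by how well it predicts follow-up. It is therefore never less precise in large samples.

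The plan uses that device for MAS but does not state it for the EMG outcomes. It also sends non-normal data to a two-sample rank test that takes no covariate, and a strictly positive amplitude may well be skewed.

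The stake is precision only. The Background section relies on RMS, iEMG and CR to assess spasm objectively, and the Discussion wants the assessments to separate neural from peripheral effects. A needlessly wide interval on these outcomes would weaken that part of the report.

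**Working it through.** **Inputs.** From the article: four assessments for RMS, iEMG and CR (Table 2), and 50 patients per group with 10% loss allowed for, so 45 per group analysed (Sample Size Calculation). The article gives no SD, effect size, reliability or power for any EMG outcome, so there is no figure of its own to reproduce here. The correlation ρ, the effect of 0.5 SD and the error variances below are assumptions, shown as ranges.

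**Step 1: does error count twice?** If each visit carries independent error variance e, the change (follow-up minus baseline) carries e + e = 2e. Yes, for a raw change.

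**Step 2: variance ratio at one follow-up visit.** Let s² be the variance at a visit and ρ the baseline-to-follow-up correlation.

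- Change score: 2s²(1−ρ)
- Baseline-adjusted: s²(1−ρ²)
- Ratio: (1−ρ²) / [2(1−ρ)] = (1+ρ)/2, which never exceeds 1

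Power at 45 per arm, two-sided 5%, assumed effect 0.5 of the SD at a visit:

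| ρ | Ratio | Power, change | Power, adjusted |
|---|---|---|---|
| 0.3 | 0.65 | 0.52 | 0.70 |
| 0.5 | 0.75 | 0.66 | 0.78 |
| 0.7 | 0.85 | 0.87 | 0.91 |
| 0.9 | 0.95 | about 1.00 | about 1.00 |

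**Step 3: effect of measurement error.** Assume error-free SD 1, error-free correlation 0.9 between any two visits, effect 0.5 of that SD, and independent error variance e at each visit. The visit variance is V = 1 + e, so ρ = 0.9/V. At one follow-up visit the change variance is 2(V − 0.9) and the adjusted variance is V − 0.81/V. For e = 0.5: V = 1.5, ρ = 0.60, change 1.20, adjusted 1.5 − 0.54 = 0.96, ratio 0.80.

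With the mean of t1–t3 as outcome, its variance is (3V + 5.4)/9. For e = 0.5 this is 1.10. The change variance is 1.10 + 1.50 − 1.80 = 0.80 and the adjusted variance is 1.10 − 0.54 = 0.56, ratio 0.70. Power at 45 per arm:

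| e | ρ | One visit: change | One visit: adjusted | Mean of t1–t3: change | Mean of t1–t3: adjusted |
|---|---|---|---|---|---|
| 0.1 | 0.82 | 0.96 | 0.98 | 1.00 | 1.00 |
| 0.25 | 0.72 | 0.81 | 0.86 | 0.94 | 0.97 |
| 0.5 | 0.60 | 0.58 | 0.68 | 0.76 | 0.89 |
| 1.0 | 0.45 | 0.36 | 0.47 | 0.50 | 0.72 |

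Averaging over three follow-up visits shrinks the follow-up error but not the baseline error. In these settings baseline adjustment therefore matters somewhat more when all visits are used.

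**Step 4: what the log scale contributes.** Simulation of t3 alone, 45 per arm, true 20% fall, log-normal amplitudes, assumed log-scale SDs of 0.5 between patients, 0.2 for visit-to-visit biology and 0.3 for re-siting:

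- raw-change t-test 38%
- Mann–Whitney 43%
- log change 53%
- log amplitude adjusted for baseline 61%

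Of the 23-point gap between 38% and 61%, 15 points come from the log scale and 8 from baseline adjustment. With re-siting SDs of 0.1 to 0.4, ρ runs from 0.25/0.30 = 0.83 to 0.25/0.45 = 0.56, so the variance ratio from adjustment alone runs from 0.92 to 0.78.

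**The case against.** The best defence is that the plan already holds most of what is asked for. A mixed model for the repeated outcomes is planned and its baseline covariate is not excluded; it simply is not restated after the MAS paragraph. Adjusted regression is planned too. Covariates and transformations for secondary outcomes are often fixed in an analysis plan, which is not shown here. The evaluator is described as blinded, so placement error should be alike in both arms. All this stands, and it keeps the point minor. It does not remove it: the article puts the change-score comparison ahead of the mixed model, and that ordering is the less efficient choice.

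A reader might infer three stronger things that the documents do not support.

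- **That electrodes are freely re-sited at every visit.** This would be read from silence. Two placement standards are named, the wording about the fullest part belongs to RMS only, and marking sites is operating detail that an article may leave to the full protocol.
- **That the EMG outcomes are analysed only as unadjusted changes.** Mixed models and covariate-adjusted regression are also planned.
- **That real effects will be hidden, with power near 38%.** That figure rests on assumed SDs, one visit and a log-normal assumption that supplies most of the gain. Step 3 shows a loss that runs from negligible to large, depending on a reliability that the article does not give.

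**Conclusion.** The point holds as a free improvement of minor severity. For RMS, iEMG and CR, the article leads with change from baseline and an unadjusted rank-test fallback, and states a baseline covariate only for MAS. Adjusting for baseline multiplies the single-visit variance by (1+ρ)/2, a reduction of 25% at ρ = 0.5, 15% at 0.7 and 5% at 0.9.

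The size depends wholly on an assumed ρ, and the formula assumes equal variance at the two visits. The direction does not depend on the value of ρ, since the ratio never exceeds 1. The issue is precision, not bias. The primary MAS analysis is unaffected.

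**What to change.** In Statistical Methods, replace the switch between change-score ANOVA and Mann–Whitney, for RMS, iEMG and CR, with one sentence along these lines: *RMS, iEMG and CR at t1, t2 and t3 will be compared between groups in the repeated-measures mixed model, with treatment, time and the outcome's own baseline value as covariate; this is the main comparison for these outcomes. If RMS or iEMG is skewed, it and its baseline will be analysed on the log scale.*

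**Cost.** One sentence, with no new data, visit, staff or procedure. The model is already planned and the baseline values are already scheduled, so the change also serves the 50 patients recruited by the time of submission. The small downside is that log-scale effects are reported as ratios rather than in raw units. The change should be recorded before unblinding. No rule on marking electrode sites is requested here; that is left to the full protocol.

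### Co-contraction ratio: the protocol does not say which of three contractions' values is maximised or that both muscles come from the same contraction, and it misreads what a fall in the ratio means

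*Protocol article*

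**What the plan says.** All of this is in the protocol article under Secondary Outcome Measures, mainly in the item on integrated electromyogram and co-contraction ratio.

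- A full-effort elbow extension is held for 10 s; its stated purpose is "to measure maximum isometric voluntary contraction (MIVC) of TM".
- Repeats: "The test is to be carried out three times, with an interval of 5 min between each application".
- The rule for reducing the three repeats to one figure is given only as "and the maximum value is to be recorded".
- Order of calculation: "The assessment includes the iEMG of the BM and TM when the elbow is stretched for MIVC, and then the CR is calculated". The formula is CR = iEMG of BM / (iEMG of BM + iEMG of TM) × 100%.
- CR also appears among the recorded quantities: "The iEMG and CR of BM and TM are to be recorded for 20 and 5 s before and after contraction".
- Interpretation: "The decrease of CR within MIVC of the elbow indicates a reduction in the strength of the biceps tendon".
- For MyotonPRO, another threefold measurement, the rule is different: "Measurement is taken once every 1 min, for three times in total, and the average is obtained".

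Table 2 schedules iEMG and CR at baseline, t1, t2 and t3.

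**The concern.** The derivation rule is stated, but it can be carried out in at least three ways:

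1. **Separate maxima.** Take the largest BM iEMG and the largest TM iEMG over the three contractions, then form the ratio.
2. **Strongest contraction.** Choose the best effort and take both muscles from it.
3. **Largest CR.** Form three ratios and keep the highest.

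These estimate different quantities. Each keeps an extreme of three values, so each depends on the spread between contractions as well as on the typical level, and each is less precise than an average. Two analysts following the text could report different CR values from the same recordings.

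The interpretation sentence is a second fault and does not depend on the first. CR is the trial's measure of antagonist co-contraction, and the Discussion says the trial is meant to clarify neural and peripheral contributions to spasticity. A wrong statement of what a CR fall shows bears directly on that aim.

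**Working it through.** **Inputs from the article.** Three contractions per assessment, a maximum rule with no named quantity, and the CR formula. The article gives no CR value or variability to reproduce.

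**Assumptions.** BM and TM iEMG are lognormal, with a contraction-to-contraction coefficient of variation (CV) and a BM–TM correlation within a contraction. Each setting was simulated with 400,000 sets of three contractions. TM iEMG stands in for strength when picking the strongest contraction.

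**Do the two maxima come from one contraction?** With correlation 0, the chance that they come from different contractions is 2/3 by symmetry (67%). With correlation 0.5 it is about 46%. This matters only under separate maxima; the other two readings always use one contraction.

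**Level and precision at true CR 40%, equal CVs, correlation 0 to 0.5.**

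| Reading | Shift in mean CR | Within-session error variance relative to mean of three |
|---|---|---|
| Separate maxima | 40.1 to 40.2, almost none | 1.7 to 2.1 |
| Largest CR, CV 20% | 44.1 to 45.8, so 4 to 6 points high | about 1.8 |
| Largest CR, CV 30% | 46.1 to 48.7, so 6 to 9 points high | about 1.8 |
| Strongest contraction, CV 20 to 30% | about 2 to 5 points low | 2.1 to 2.6 |

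For separate maxima at CV 20%, the variance ratio follows from the standard deviations: (4.99/3.83)² = 1.70 at correlation 0 and (3.93/2.72)² = 2.09 at correlation 0.5. Over a wider set of assumptions the range for all three readings is about 1.7 to 2.8.

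**Unequal CVs, true CR 30%, correlation 0.5.** Separate maxima do shift when the muscles differ in variability. BM CV 0.3 with TM CV 0.1 gives 32.9; BM 0.1 with TM 0.3 gives 27.6. Across all settings run at true CR 30% (correlation 0 to 0.8), separate maxima give 27.6 to 34.0, the mean of three CRs 28.6 to 31.2, and CR from mean iEMGs 29.5 to 30.4.

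**Total variance.** Differences between patients dilute the precision loss. With an assumed between-patient SD of 5 points, the ratio of total variances for separate maxima is (25 + 4.99²)/(25 + 3.83²) = 49.9/39.7 = 1.26. With 15 points and correlation 0.5 it is (225 + 3.93²)/(225 + 2.72²) = 240.4/232.4 = 1.03. The increase is therefore about 3 to 26%, not 70 to 109%.

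**Interpretation sentence.** With BM held fixed, BM/(BM + TM) falls whenever TM rises. For illustration, BM:TM of 40:60 gives 40%. If TM rises by 20% to 72 and BM stays at 40, CR is 40/112 = 35.7%. Biceps activity has not changed, yet the sentence would read this as a change in the biceps. The article also describes iEMG as muscle discharge per unit time, which is not tendon strength.

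**The case against.** The best defence is that the passage describes a maximal-effort test, so the natural reading is best of three, with both muscles taken from that effort. CR then comes from a real contraction. This is plausible, and the text never says that the maxima are taken separately. It also never says that they are paired, and CR is itself listed as a recorded quantity, so the ambiguity stands.

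The MyotonPRO contrast is weak. That is a passive reading in a relaxed patient, and choosing the best of several voluntary efforts can serve a different aim. Averaging the two measurements differently is not in itself an inconsistency.

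A reader might infer that the maximum rule can create a false treatment effect on CR. One can construct such a case: at true CR 30% and correlation 0.5, with TM CV 0.1 in both arms and BM CV 0.3 in one arm and 0.1 in the other, separate maxima differ by 32.9 − 30.0 = 2.9 points. That requires treatment to change contraction variability while leaving co-contraction alone, and nothing in the article supports it. The same rule applies in both randomised arms, so with equal variability the shift cancels.

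On the interpretation sentence, it is fair that the article calls CR a proportion and collects iEMG at every visit, so a careful reader could see which muscle changed. The sentence still states something the formula does not show.

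**Conclusion.** Two faults hold. First, the CR rule does not identify the value maximised or require BM and TM to be paired. Each available reading is less precise within a session than the mean of three, by a factor of about 1.7 to 2.8 in error variance, and two of them move the level of CR: the largest CR upward by about 4 to 9 points, the strongest contraction downward by about 2 to 5. These sizes rest on assumed CVs, correlations and a true CR of 40%. The loss in total variance is smaller.

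Second, the statement about the biceps tendon is wrong under the protocol's own formula, and this needs no assumption.

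It does not follow that CR as planned describes no real contraction, since that arises only under separate maxima. Nor is bias between arms shown. The point concerns one secondary outcome; the MAS primary outcome is untouched. It should be corrected before analysis.

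**What to change.** State that CR is calculated within each of the three contractions from the BM and TM iEMG of that contraction, and that the mean of the three is analysed. CR from the mean BM and mean TM iEMG is an acceptable alternative and was slightly more stable in the settings above. Treat BM and TM iEMG by the same averaging rule. If the best effort is deliberately wanted, name the criterion that selects it and take both muscles from that one contraction.

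Replace the interpretation sentence with: *A fall in CR indicates a lower share of biceps activity; it is attributed to the biceps only if BM iEMG also falls.*

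Cost: no extra testing, because three contractions are already performed. Averaging does bring in less than maximal efforts, which changes the quantity somewhat. Trial Status reports 50 of the planned 100 patients recruited at submission; their values can be recomputed only if all three recordings were kept. If only the recorded maximum survives, the rule actually used for those patients should be documented.
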